### In Relation to Treatment

#### Design: Random clinical trial

The subjects included in the study will be randomized (with a hidden sequence) to two sets of experimental conditions:

1. – Protocolized treatment based on active and passive joint repositioning, stabilization exercises, stretching of the periarticular shoulder muscles and postural reeducation.

2. – The previously described protocolized treatment with the addition of dry needling of active MTrPs on the supraspinatus, infraspinatus, subscapularis and teres minor muscles using Hong's fast-in and fast-out technique, once for each active MTrP and accompanied by a cold spray to reduce the painful post-needling sensation. Only one needling will be performed in each session with an interval of 8 days between sessions.

The purpose of these treatment methods is to isolate the efficacy of dry needling in the treatment of rotator cuff tendonitis and/or SIS.

Training and standardization sessions will be held for both protocols so that the intervention will be the same for all subjects in the study.

The treatment will consist of 10 physiotherapy sessions and the measuring of dependent variables will be made during the initial visit and at the end of the treatment. The final and follow-up measuring will be performed by a blind evaluator.

The sample size is 132 patients (with and error of 0.05 and a power of 80%, if a correlation of 0.25 of the sample size is taken to be 120 patients; expecting a 10% attrition, the necessary sample size would be 132 patients). The patients will be randomized to include 66 subjects in each therapy method.

The study variables related to treatment are shown on the table 2:

**Table 2 T2:** Study Variables Related to Treatment

INDEPENDENT VARIABLE	DEPENDENT VARIABLE	
THERAPY METHOD	Joint restriction by	Flexion-extension movements
		
	digital inclinometer	Abduction-adduction movements
		
		Lateral-medial rotation movements
	
A. Protocolized treatment	Pain on elevation in the scapular plane	VAS scoring
		
		Location of pain
	
B Protocolized treatment + dry needling of MTrPs	Function Constant Test	
	
	Existence of active MTrPs by algometry	Supraspinatus
		
		Infraspinatus
		
		Subescapularis
		
		Teres minor

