### AIMS Regarding Treatment

- Evaluation of the efficacy of dry needling of active MTrPs in the treatment of SIS and rotator cuff tendonitis compared to habitual clinical protocols.

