### In Relation to Diagnosis

Design: Transversal descriptive study

Study subjects: Patients belonging to 5 health centres in the city of Zaragoza (Spain) over the age of 18 who are diagnosed with rotator cuff tendonitis and/or SIS by a general practitioner (GP) and who give their consent after being informed about participation in the study. The minimum number of patients to be recruited is 132.

Inclusion criteria:

- Diagnosis of rotator cuff tendonitis and/or SIS by GP.

- Functional limitation and pain above 50% of the range of movement in flexion, abduction, and elevation in the scapular plane.

Exclusion criteria:

- Previous surgery for SIS

- Great limitation, pain or sudden loss of strength after suffering a traumatism that suggests another serious condition.

- Other red flag signs indicating systemic disease.

- Inability to attend intervention sessions or refusal to participate.

Study variables related to diagnosis are shown on the table 1:

**Table 1 T1:** Study Variables Related to Diagnosis

General variables	Age
	Sex
	Occupation
Pain history	Period of evolution
	Background

Previous treatments	Drug type
	Period administered
	Evolution with medication

Elevation in the scapular plane	Score on Visual Analogical Scale (VAS) Location of pain

Joint restriction (digital inclinometer)	Flexion-extension movements
	Abduction-adduction movements
	Lateral-medial rotation movements

Constant Test	

Provocation tests	Neer manoeuvre
	Jobe's test
	Hawkins test
	Yocum test
	Patte's test
	Gerber test
	Drop arm test. Painful arc test

MTrP existence by means of:	Physical examination
	Ultrasonography

The following confusion variables will be controlled: osteophytes on the lower face of the acromion, existence of latent trigger points on serratus anterior, biceps braquialis and both pectoralis, sports activity and occupation involving lifting of upper limbs above 90° of flexion or abduction.

Data analysis: a descriptive analysis will be made of the defined variables followed by a bivariate analysis by means of Pearson's r, Spearman's rho or Kendall's tau-b correlations. Multivariate analysis will be performed using logistic regression, including the variables that had a significant result in the bivariate analysis. A correlation will be established between diagnosis of SIS and rotator cuff tendonitis, positive provocation tests, existence of active MTrPs and the diagnostic results obtained with US.

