## Data analysis

- Multiple variance analysis techniques to evaluate the differences between pre- and post-treatment values in dependent variables for both groups. The variables with significant basal moment differences between both groups (despite randomization) that may constitute a factor of confusion will be controlled.

- Multivariate analysis to determine the influence of the treatment programme on the evolution of symptoms. Routinely used techniques in clinical trials will be employed, such as intention to treat (to manage withdrawals from either group) and survival curves, among others.

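### The trial's 80% power and 5% error come from a test of one correlation of 0.25 and are tied to no named efficacy outcome among the ten rows of Table 2

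*Protocol article*

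**What the plan says.** The sample size paragraph stands under the heading for the randomised trial. It sets the operating characteristics ("with and error of 0.05 and a power of 80" per cent), the effect size ("if a correlation of 0.25 of the sample size is taken to be 120 patients"), the allowance for loss ("expecting a 10% attrition, the necessary sample size would be 132 patients") and the allocation ("The patients will be randomized to include 66 subjects in each therapy method"). The two correlated variables are not named, and no treatment difference is given.

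The cross-sectional part, In Relation to Diagnosis, uses the same total: "The minimum number of patients to be recruited is 132". It is also the only part that plans correlations: "bivariate analysis by means of Pearson's r, Spearman's rho or Kendall's tau-b correlations".

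The single treatment aim is "Evaluation of the efficacy of dry needling of active MTrPs in the treatment of SIS and rotator cuff tendonitis compared to habitual clinical protocols", with no outcome attached. The Data analysis section plans "Multiple variance analysis techniques to evaluate the differences between pre- and post-treatment values in dependent variables for both groups". Table 2 lists those dependent variables in ten rows under four domains:

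- joint restriction (three pairs of movements);
- pain on elevation (VAS score and location);
- function (Constant test);
- active trigger points (four muscles).

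No row is marked as primary.

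**The concern.** A power statement is useful only if it names the test and the outcome to which it applies. Here the effect measure is a correlation, while the planned comparison of arms is a variance analysis of several outcomes, and the text gives no link between the two. A reader cannot tell which result would establish efficacy. One favourable row out of ten could be presented as success after the data are seen. Equally, a null result could be read as evidence against effects that the trial had little power to detect on any single outcome.

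**Working it through.** **Inputs.** From the sample size paragraph: error 0.05, power 80%, r = 0.25, N = 120 before attrition, 10% attrition, 132 in total, 66 per arm. From Table 2: ten rows in four domains. The documents do not give the sidedness of the test, the correlation between outcomes, or the correlation of each outcome with its baseline; these are assumed below.

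**1. Reproducing the stated size.** For a two-sided test of one correlation against zero:

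- t form: n = (1.960 + 0.842)² × (1 − r²)/r² + 2 = 7.849 × 0.9375/0.0625 + 2 = 119.7, so 120.
- Fisher z form: n = ((1.960 + 0.842)/atanh 0.25)² + 3 = 123.3. With n = 120, power is 78.9%.
- One-sided versions need about 95 to 98 and do not match.
- Attrition: 120 × 1.10 = 132. Dividing by 0.9 would give 134, a trivial difference.

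The arithmetic is sound, and it is that of one two-sided correlation test.

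**2. Rereading it as a two-arm comparison.** If r is assumed to be the point-biserial correlation between arm and one continuous outcome, d = 2r/√(1 − r²) = 0.50/√0.9375 = 0.516. The power of an unadjusted two-sample t-test with 60 evaluable per arm, two-sided 0.05, one outcome, is then:

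| Standardized difference | Power |
|---|---|
| 0.516 | 80.1% |
| 0.4 | 58% |
| 0.3 | 37% |

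**3. Ten rows each tested at 0.05.** If independent, the family-wise error is 1 − 0.95¹⁰ = 40.1%. With an assumed common correlation, simulation gives:

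| Common correlation | At least one false positive |
|---|---|
| 0 | 40% |
| 0.3 | 35% |
| 0.5 | 29% |
| 0.7 | 21% |
| 0.9 | 13% |

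Counting the four domains in place of the ten rows, and assuming independence, gives 1 − 0.95⁴ = 19%.

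**4. Cost of controlling the error instead.** With Bonferroni over ten (alpha 0.005), power at d = 0.516 with 60 per arm and no baseline adjustment is 49% by the exact t calculation (51% by the normal approximation).

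**5. Effect of baseline adjustment.** ANCOVA reduces the residual standard deviation by √(1 − ρ²), where ρ is the correlation between baseline and final value. With ρ assumed to be 0.3, the difference detectable with 80% power is 0.516 × √0.91 = 0.49. With ρ = 0.7 it is 0.516 × √0.51 = 0.37.

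**The case against.** Several points on the other side carry weight.

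- **The size may be adequate.** Step 2 shows that 60 per arm gives 80% power for a half-standard-deviation difference on one outcome. A reader might infer that the trial is underpowered or its sample size miscalculated. The documents support neither.
- **The origin of 0.25 is not stated.** A reader might infer that the figure was borrowed from the diagnostic study, given the shared 132 and the correlations planned only there. That is plausible, but the calculation is printed under the randomised trial, directly before the 66/66 split, so it remains inference.
- **Ten separate 5% tests are not what the text says.** The analysis wording may mean MANOVA, whose single global test would hold 5% for the global null. This reading is possible, but the article does not state it. A global test would not protect claims on individual outcomes, and the printed calculation does not size a multi-outcome global test either.
- **40% is the worst case.** Three ranges of movement in one shoulder, pain and function are unlikely to be independent, so the range in step 3 is the fair statement.
- **The t-test figures do not fit every row.** Pain location is not a continuous score, and the presence of trigger points in four muscles may be yes/no. The unadjusted figures also understate the power of an analysis that uses baseline values.
- **An unseen analysis plan may settle multiplicity.** It may well do so. But the article itself prints a sample size basis and an outcome table that do not connect, and the primary outcome and the basis of the sample size belong in the protocol.

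**Conclusion.** The concern holds in a limited form. The stated 80% power and 5% error are correct for one two-sided test of r = 0.25 but are attached to no planned comparison of the arms, and no Table 2 outcome is primary. What counts as evidence of efficacy is therefore open to selection.

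If all ten rows were tested at 0.05, the chance of at least one false positive would be about 13% to 40%, on assumed correlations of 0.9 to 0. The 80% power can be carried over to the trial only by assuming that r = 0.25 means d = 0.52 on a single outcome with 60 evaluable per arm. The defect is the missing link between calculation and outcome. It does not show that 132 patients are too few.

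**What to change.** 1. Before unblinding, name one outcome already collected in Table 2 as primary. The choice is the sponsor's; the Constant score is one example. Analyse it by ANCOVA on its baseline value and label all other outcomes secondary.
2. State which variables the correlation of 0.25 refers to.
3. Restate the power along these lines: *60 evaluable patients per arm give 80% power for a standardized difference of 0.52 on the primary outcome without baseline adjustment (about 0.49 to 0.37 with ANCOVA if the correlation with baseline is assumed to be 0.3 to 0.7).* This wording suits a continuous primary outcome; a yes/no outcome would need its own calculation.

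The cost is a change of wording, with no extra patients, visits or measurements. The downside is that the remaining outcomes become supportive and cannot carry the efficacy claim by themselves.

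### The attrition allowance is slightly too small: 132 patients less 10% leaves 118 to 119, below the plan's own 120, and holding 120 needs 134

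*Protocol article*

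**What the plan says.** The only planning calculation in the Protocol article is one sentence under In Relation to Treatment (Design: Random clinical trial). It opens with the total, "The sample size is 132 patients", and gives the operating characteristics as "with and error of 0.05 and a power of 80" (per cent). The base number follows: "if a correlation of 0.25 of the sample size is taken to be 120 patients". The allowance for losses is then added: "expecting a 10% attrition, the necessary sample size would be 132 patients". The next sentence fixes the allocation: "The patients will be randomized to include 66 subjects in each therapy method".

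The same total appears in the section In Relation to Diagnosis: "The minimum number of patients to be recruited is 132".

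The article does not say whether the 5% is one-sided or two-sided, which test or formula was used, or which two variables the correlation of 0.25 concerns.

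**The concern.** The sentence treats 132 as the number that still delivers 120 patients once 10% are lost. It does not, because the 10% was taken of the 120 and added on. Losses occur among those recruited, so the 120 should have been divided by 0.9. The sentence therefore contradicts its own figures, whatever formula produced the 120.

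At stake is whether the stated power and the claim that 132 covers 10% attrition are true as written. No other planning figures are given, and the total carries through to the 66 per arm and to the recruitment minimum of the diagnostic part.

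**Working it through.** **Inputs.** From the sample-size sentence: error 0.05, power 80%, r = 0.25, base size 120, attrition 10%, total 132, 66 per arm. Assumption: the 5% is two-sided. One-sided versions of the calculations below give 95 to 99 patients, far from 120, so two-sided is the reading that fits.

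**Step 1: reproduce the 120.** With the two-sided test of a correlation based on the noncentral t (the point-biserial or fixed-regressor case, equivalent to a two-group t test), the noncentrality is √(N·r²/(1 − r²)).

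- r²/(1 − r²) = 0.0625/0.9375 = 0.0667.
- At N = 120: √(120 × 0.0667) = √8 = 2.83 on 118 degrees of freedom, power 80.1%.
- At N = 119: power 79.8%.

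So 120 is the smallest adequate size by this method.

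Fisher's z gives a slightly larger figure: ((1.960 + 0.842)/atanh 0.25)² + 3 = (2.8016/0.2554)² + 3 = 120.3 + 3 = 123.3, so 124. Its bias-corrected form with a t critical value gives 123.

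**Step 2: reproduce the 132.** 120 × 1.10 = 132.

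**Step 3: apply the 10% loss to the number recruited.**

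- Overall: 132 × 0.9 = 118.8. By arm: 66 × 0.9 = 59.4, so 59 complete in each arm, 118 in all.
- Loss that 132 can absorb while keeping 120: (132 − 120)/132 = 12/132 = 9.1%.
- Total that keeps 120 after a 10% loss: 120/0.9 = 133.3, so 134, or 67 per arm. Check: 134 × 0.9 = 120.6.

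**Step 4: power for r = 0.25, two-sided 5%.**

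| Evaluable | Noncentral t | Fisher z, bias-corrected | Fisher z |
|---|---|---|---|
| 118 | 79.4% | 78.5% | 78.2% |
| 119 | 79.8% | 78.9% | 78.6% |
| 120 | 80.1% | 79.2% | 78.9% |
| 132 (no loss) | 83.8% | 82.9% | 82.7% |

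For example, Fisher z at 118 is Φ(0.2554 × √115 − 1.960) = Φ(0.779) = 78.2%. By the method that reproduces 120, the attrition slip costs 80.1 − 79.4 = 0.7 points at 118 and 80.1 − 79.8 = 0.3 points at 119.

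**The case against.** Three arguments favour leaving the figure alone.

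- **The attrition may not bear on the correlation.** The correlation analyses named in the article belong to the cross-sectional diagnostic part, which has no follow-up. A patient who later withdraws from treatment need not be lost to it. With all 132, power for r = 0.25 is 82.7% to 83.8%. The 132 is also described there as a minimum.
- **The trial part plans an intention-to-treat analysis to deal with withdrawals**, so those who leave need not all be lost.
- **The slip is smaller than the uncertainty in its inputs.** Two patients in 132 is 1.5%, and neither a planning correlation of 0.25 nor a 10% attrition guess is known that closely. A plain normal approximation to the equivalent two-group comparison (d = 0.516) even gives 118 in total.

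The first two do not rescue the statement, because the sample-size sentence itself applies the 10% loss to this calculation and gives 132 as the number that covers it. The normal approximation does not reproduce the plan's 120, so it cannot be taken as the plan's method. What stands is that the effect is small.

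A reader might go further and infer that 120 is itself too low, that r = 0.25 needs 123 or 124 evaluable and 124/0.9 = 137.8, so 138, recruited, and that the power delivered is about 78%. The article does not support this. Those figures follow from Fisher z, and the article names no formula. A standard two-sided calculation gives exactly 120, and about 78% is the low end of a range of 78.2% to 79.8%.

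**Conclusion.** The point holds as a minor arithmetic error. By the plan's own numbers, 132 recruited with 10% attrition leaves 118 to 119 evaluable and not 120; the number that keeps 120 is 134, two more than stated. That much needs no assumption about the test.

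The effect on power does depend on assumptions: two-sided 5%, r = 0.25, and a formula the article does not name. Under those, power at 118 is about 79.4% by the noncentral t and about 78.2% by Fisher z, so at most about 2 points below the stated 80%. The base figure of 120 is sound under the former and is not a finding. Nothing here threatens the validity of the trial.

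**What to change.** Keep 132 (66 per arm) and correct the sentence, for example: with 132 recruited and 10% attrition, about 118 patients are expected to be evaluable, giving about 79.4% power to detect a correlation of 0.25 at a two-sided 5% level (noncentral t). If Fisher z was the method used, the figure to state is about 78.2%. Name the formula and the sidedness in either case, after confirming them against the calculation that was run.

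If the plan is to keep 120 evaluable after a 10% loss, the total becomes 134, with 67 per arm, and the minimum in the section In Relation to Diagnosis should be changed to match. A target of 124 evaluable and 138 recruited applies only if Fisher z is the intended method.

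The first option costs one sentence and a stated power slightly below 80%, with no change to the design. The second costs two more patients.

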## Data analysis

- Multiple variance analysis techniques to evaluate the differences between pre- and post-treatment values in dependent variables for both groups. The variables with significant basal moment differences between both groups (despite randomization) that may constitute a factor of confusion will be controlled.

- Multivariate analysis to determine the influence of the treatment programme on the evolution of symptoms. Routinely used techniques in clinical trials will be employed, such as intention to treat (to manage withdrawals from either group) and survival curves, among others.

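### Covariates for the treatment comparison are chosen by baseline significance tests on top of a pre/post difference analysis; ANCOVA on each outcome's baseline, fixed in advance, would be more precise at no cost

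*Protocol article*

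**What the plan says.** The first bullet of the article's Data analysis section, which covers the randomised trial, names the method as "Multiple variance analysis techniques to evaluate the differences between pre- and post-treatment values in dependent variables for both groups". It then fixes how covariates enter: "The variables with significant basal moment differences between both groups (despite randomization) that may constitute a factor of confusion will be controlled". A variable must therefore meet two conditions: a significant baseline difference between arms, and a judgement that it may confound.

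The second bullet plans "Multivariate analysis to determine the influence of the treatment programme on the evolution of symptoms" and names no covariates. The confounding variables listed under In Relation to Diagnosis belong to the cross-sectional study. No covariate is named in advance for the treatment comparison.

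Under Design: Random clinical trial, "the measuring of dependent variables will be made during the initial visit and at the end of the treatment", so every outcome has a baseline value. Table 2 gives therapy method as the independent variable.

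**The concern.** Allocation is random, so any baseline difference between arms is due to chance. Testing it for significance says nothing about how strongly the variable predicts outcome, and prediction is what makes adjustment worthwhile. Under the stated rule, a strongly prognostic variable with p = 0.06 is left out. The model is settled only once the data are seen, with an undefined judgement about confounding added.

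The rule sits on an analysis of pre/post differences. If this means repeated-measures analysis of variance, then with two time points the group-by-time test is the change-score test. A change score subtracts the whole baseline value, although the baseline predicts only a fraction rho of it. The estimate then depends on whatever imbalance randomisation happened to produce, and precision is lost. The most useful covariate, the outcome's own baseline, is already collected but enters as a covariate only if it happens to differ significantly.

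**Working it through.** **Inputs from the article (Design: Random clinical trial).** Alpha and power: "with and error of 0.05 and a power of 80"% (sidedness not given). Effect: "if a correlation of 0.25 of the sample size is taken to be 120 patients". Attrition: "expecting a 10% attrition, the necessary sample size would be 132 patients". Allocation: "The patients will be randomized to include 66 subjects in each therapy method".

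**Assumed.** rho is not in the document; 0.3, 0.5 and 0.7 are shown. Pre and post SDs are taken as equal.

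**1. The plan's own figure.** Two-sided: (1.96 + 0.8416)² × (1 − 0.25²)/0.25² + 2 = 7.849 × 15 + 2 = 119.7, so 120. Then 120 × 1.10 = 132. Both are reproduced.

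**2. The correlation as a difference between arms.** d = 2r/√(1 − r²) = 0.50/0.968 = 0.516 SD. This conversion is made here; the article states no between-arm difference.

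**3. What escapes the test.** The SE of a baseline difference is √(2/66) = 0.174 SD, so differences up to 1.96 × 0.174 = 0.34 SD are not significant (0.36 SD with 60 per arm). Any one covariate is flagged in about 5% of trials. The median absolute imbalance is 0.6745 × 0.174 = 0.12 SD.

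**4. Conditional error of the change score.** Given a baseline imbalance, the contrast shifts by (1 − rho) × imbalance, in the opposite direction.
- Boundary case, 0.34 SD: 0.24, 0.17 and 0.10 SD at rho 0.3, 0.5 and 0.7.
- Typical case, 0.12 SD: 0.5 × 0.12 = 0.06 SD at rho 0.5.

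**5. Precision.** In units of SD²(1/n₁ + 1/n₂), the variance is 2(1 − rho) for the change score and 1 − rho² for ANCOVA. The ratio is (1 + rho)/2. Power with 60 per arm is Φ(0.516/√(v × 2/60) − 1.96), with v the variance factor:

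| rho | v, change | v, ANCOVA | ratio | power, change | power, ANCOVA |
|---|---|---|---|---|---|
| 0.3 | 1.40 | 0.91 | 0.65 | 0.67 | 0.84 |
| 0.5 | 1.00 | 0.75 | 0.75 | 0.81 | 0.90 |
| 0.7 | 0.60 | 0.51 | 0.85 | 0.95 | 0.98 |

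Put as sample size, ANCOVA matches the precision of a change score in 120 patients with 78, 90 or 102.

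**6. The rule itself.** Simulation: 40,000 trials per setting, 60 per arm, change score unless the outcome's baseline differs at p < 0.05, then ANCOVA. The confounder condition was taken as met.
- No true effect: overall rejection is 4.2%, 4.3% and 4.6% at rho 0.3, 0.5 and 0.7.
- No true effect, non-significant imbalance above 0.25 SD (about 12% of trials): the change score rejects in 11.6%, 9.3% and 8.1%; ANCOVA in 5.1%, 5.6% and 5.7%.
- True effect 0.5 SD: power is 64.2%, 78.4% and 94.4% under the rule, against 81.0%, 87.7% and 96.8% for ANCOVA throughout.

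**The case against.** The strongest reply is that the planned comparison is valid. Averaged over randomisations the change-score contrast is unbiased, and the two-stage rule does not inflate type I error. At the derived effect of 0.52 SD, the change score reaches 80% power at rho 0.5 and above; a clear shortfall appears only at the low assumed rho of 0.3. The wording on variance analysis does not exclude ANCOVA, and an article may leave the form of the model to a fuller plan. All of this stands, and it limits the severity. It does not rescue the selection rule, which the article states outright.

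Four stronger readings are tempting and are not supported:
- **Only within-group tests are planned.** Table 2 makes therapy method the independent variable, and the second analysis bullet aims at the influence of the treatment programme. The natural reading is a comparison between arms.
- **An irrelevant variable with p = 0.04 would be adjusted for.** The rule also requires that the variable could confound.
- **Chance imbalance is left uncorrected.** That holds for other covariates that miss significance. For the outcome's own baseline, the change score corrects too much.
- **The estimate is typically off by a third of the planned effect.** 0.17/0.52 is about one third, but it combines a boundary imbalance, reached in about 5% of randomisations, with an assumed rho and a derived effect size.

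**Conclusion.** The point holds as one of efficiency and prespecification. Selecting covariates by baseline significance is uninformative in a randomised trial, leaves prognostic variables unadjusted when they miss significance, and lets the data settle the model. Combined with change scores, it costs about 17 percentage points of power at rho 0.3, 10 at 0.5 and 2 at 0.7 (from the table in the working), and it makes the result depend on the imbalance that happens to occur. A reader might infer that the trial's conclusions would be invalid or its error rate inflated; the calculations do not support that.

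The sizes rest on rho, which the document does not give, on equal SDs before and after treatment, on 60 evaluable patients per arm, and on converting r = 0.25 to 0.52 SD. At rho of 0.7 or above the gain in power is small. The objection to the selection rule does not depend on rho.

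**What to change.** Delete the sentence that ties adjustment to significant baseline differences. In its place state, for example: *Each continuous outcome is compared between arms at the end of treatment by ANCOVA, with the baseline value of that outcome as covariate, together with any stratification factor or other prognostic covariate named here in advance. Baseline significance tests are not used to choose covariates. The adjusted difference between arms is reported with its 95% confidence interval.*

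The cost is a change of wording. The baseline values are already collected, and neither the sample size nor the visit schedule changes. The change should be recorded before outcome data are seen by arm.

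### Variance analysis of pre/post differences is stated for outcomes of differing scale, and survival curves are named with no time-to-event outcome

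*Protocol article*

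**What the plan says.** The first bullet of the Data analysis section of the protocol article gives the main comparison: "Multiple variance analysis techniques to evaluate the differences between pre- and post-treatment values in dependent variables for both groups". It adds that variables differing significantly between the arms at baseline, and able to confound, will be controlled.

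The second bullet plans a further analysis, "Multivariate analysis to determine the influence of the treatment programme on the evolution of symptoms", without naming a model. It then says that techniques in routine trial use will be employed, "such as intention to treat (to manage withdrawals from either group) and survival curves, among others".

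The dependent variables are listed under that column heading in Table 2. They are three pairs of inclinometer movements, pain on elevation by VAS, "Location of pain", the Constant test, and "Existence of active MTrPs by algometry" in four muscles.

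On timing, the treatment design section says that "the measuring of dependent variables will be made during the initial visit and at the end of the treatment". The next sentence reads "The final and follow-up measuring will be performed by a blind evaluator", and no time is given for the follow-up.

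**The concern.** One method is attached to a list of outcomes that do not share a scale. Subtracting a baseline location of pain from a final one gives no number, so the stated analysis cannot be carried out for that row. For MTrP existence the answer depends on what is analysed: a present/absent finding or an algometer reading. This matters because the four muscles are the ones needled in the dry-needling arm, so these rows lie closest to the target of the intervention.

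Survival curves need an event, a time origin and observed event times. Table 2 contains no outcome of that kind.

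The handling of baseline is a related weakness. A change score makes only a fixed correction for the baseline value of the outcome, and the plan adds covariates only where a baseline difference is significant. In a randomised trial such differences arise by chance. The rule therefore chooses covariates by the luck of the allocation and not by how well they predict outcome, and the baseline value of each outcome is usually a strong predictor.

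**Working it through.** The plan gives no figure on this point to reproduce. Its sample size (120, raised to 132) rests on a correlation of 0.25 and does not change with anything below. The check sets Table 2 against the Data analysis bullets.

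**Step 1. Scale of each outcome row in Table 2.**

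| Outcome | Rows | Scale | Fit of variance analysis of pre/post differences |
|---|---|---|---|
| Inclinometer movements | 3 | continuous | usable |
| VAS on elevation | 1 | treated as continuous | usable |
| Constant test | 1 | treated as continuous | usable |
| Pain location | 1 | nominal | no meaning |
| MTrP existence, four muscles | 4 | present/absent, or algometer threshold | depends on which is analysed |

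Total: 3 + 1 + 1 + 1 + 4 = 10 rows.

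- If the algometer threshold is analysed, 1 of 10 rows does not fit.
- If presence is analysed, 1 + 4 = 5 of 10 rows are categorical: one cannot be analysed as stated, and four can be, but not well.

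**Step 2. What happens if MTrP presence is coded 0/1.** The individual difference, post minus pre, is −1, 0 or 1. Its mean in an arm is p(post) − p(pre), and the contrast between arms is

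[pB(post) − pB(pre)] − [pA(post) − pA(pre)].

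This is a legitimate difference in changes of proportions. The weakness is that a muscle with an active MTrP at baseline can only score −1 or 0, and one without can only score 0 or 1. The listed inclusion criteria do not require an active MTrP, so both kinds may occur, and the mean change mixes them. The four muscles also belong to the same patient, so their results are not independent.

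**Step 3. Change score against ANCOVA for the continuous rows.** Let the standard deviation σ be the same at both times and the pre/post correlation be ρ. The plan gives no value of ρ.

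- Residual variance, change score: 2σ²(1 − ρ)
- Residual variance, ANCOVA: σ²(1 − ρ²)
- Ratio, ANCOVA to change score: (1 − ρ²) / [2(1 − ρ)] = (1 + ρ)/2

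The ratio is below 1 for every ρ below 1, so ANCOVA is at least as precise with the same data. If the variance analysis is a repeated-measures model with two times, its group-by-time test is the same comparison as the change score.

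**Step 4. Survival curves.** None of the ten rows is a time to an event, and no event, time origin or censoring rule is named. For the two dated measurements, any change is known only to have happened between them. A curve built on these would restate the proportion at the end of treatment. No event count or power can be computed, because the article gives no event rate, hazard ratio or follow-up time.

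**The case against.** The case on the other side has five parts.

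- **Binary outcomes.** A mean difference of a 0/1 variable is a valid summary, and with 66 patients per arm a mean-based test comes close to a comparison of proportions unless these are extreme. This stands. A reader might infer that variance analysis is invalid for MTrP existence; step 2 shows that it is only poorly suited.
- **Algometry.** An algometer gives a continuous reading, and Table 2 names it where Table 1 names physical examination and ultrasonography. This also stands. A reader might infer that half of the outcomes lack a valid analysis. That count needs the present/absent reading, which the label suggests but the text does not settle, and it also needs the binary analysis to be invalid, which it is not.
- **Follow-up.** A follow-up measurement is mentioned. A reader might infer that there is only one post-baseline visit, so that any survival curve has a single step. The undated follow-up prevents that conclusion; it holds only for the two dated times.
- **Survival curves as an example.** They appear in an open list and are not tied to a Table 2 outcome. Time to withdrawal could be plotted, and an event definition may sit in a fuller document. This stands in part. The sentence links withdrawals to intention to treat and not to a curve, and an undefined event alone would be close to detail that an article may omit. What remains is a named method with no matching outcome in the article's own table.
- **Other models.** The treatment part also plans an unnamed multivariate analysis, and the diagnostic study states "Multivariate analysis will be performed using logistic regression, including the variables that had a significant result in the bivariate analysis". A categorical method is therefore not excluded. Even so, none is stated for the trial outcomes, and the one method tied to the dependent variables does not fit all of them.

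**Conclusion.** The point holds in limited form. Variance analysis of pre/post differences cannot be done meaningfully for pain location, which is 1 of the 10 rows in Table 2. It is poorly suited, though not invalid, for the four MTrP rows if presence is analysed, and it can fit if the algometer threshold is analysed. Survival curves are named although no Table 2 outcome is a time to an event and the only dated measurements are the first visit and the end of treatment.

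The movements, VAS and Constant test keep a workable analysis, so the trial's treatment comparison is not undermined. The clearest gain from a change is in the handling of baseline, where a better method uses data already planned.

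The conclusion assumes that the dependent variables in the first Data analysis bullet are those under that heading in Table 2, and that pain location is recorded as a category.

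**What to change.** Reword the two Data analysis bullets as follows.

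- **Continuous outcomes** (movements, VAS, Constant test, and the algometer threshold if that is used): compare the end-of-treatment value between arms by ANCOVA. Always include the baseline value of the same outcome, whether or not the arms differ significantly at baseline.
- **MTrPs:** state whether presence or threshold is analysed. If presence, use logistic regression adjusted for baseline status, with a patient-level random effect or generalised estimating equations to account for four muscles per patient.
- **Pain location:** compare between arms as a categorical variable, by cross-tabulation or a multinomial model.
- **Survival curves:** drop them unless an event with observed times is defined.

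The cost is the rewording of two bullets and slightly more analysis work. No new data are needed, unless the survival curves are kept and an event has to be recorded for them.
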